## Abstract

**Background:**

Maternal obesity before and during pregnancy predicts maternal and infant risks of obesity and its associated metabolic conditions. Dietary and physical activity recommendations during pregnancy as well as weight monitoring are currently available in the Chilean primary health care system. However some of these recommendations are not updated and most of them are poorly implemented. We seek to assess the effectiveness of an intervention that enhances the implementation of updated nutrition health care standards (diet, physical activity, and breastfeeding promotion) during pregnancy on maternal weight gain and infant growth.

**Methods:**

*Design & Setting*: Cluster randomized controlled trial. The cluster units will be 12 primary health care centers from two counties (La Florida and Puente Alto) from the South-East Area of Santiago randomly allocated to: 1) enhanced nutrition health care standards (intervention group) or 2) routine care (control group).

*Participants:* Women seeking prenatal care before 15 weeks of gestation, residing within a catchment area of selected health centers, and who express that they are not planning to change residence will be invited to participate in the study. Pregnant women classified as high risk according to the Chilean norms (i.e age <16 or >40 years, multiple gestation, pre-gestational medical conditions, previous pregnancy-related issues) and/or underweight will be excluded.

*Intervention:* Pregnant women who attend intervened health care centers starting at their first prenatal visit will receive advice regarding optimal weight gain during pregnancy and diet and physical activity counseling-support. Pregnant women who attend control health clinics will receive routine antenatal care according to national guidelines. We plan to recruit 200 women in each health center. Assuming a 20 % loss to follow up, we expect to include 960 women per arm.

*Main outcome measures:* 1) Achievement of adequate weight gain based on IOM 2009 recommendations and adequate glycaemic control at 24-28 weeks of pregnancy according to ADA 2011, and 2) healthy infant growth during the first year of age based on WHO standards.

**Discussion:**

We expect that the intervention will benefit the participants in achieving adequate weight gain & metabolic control during pregnancy as well as adequate infant growth as a result of an increased impact of standard nutrition and health care practices. Gathered information should contribute to a better understanding of how to develop effective interventions to halt the maternal obesity epidemic and its associated co-morbidities in the Chilean population.

**Trial registration:**

Clinicaltrials.gov Identifier: NCT01916603

## Background

Obesity and related chronic diseases [cardiovascular diseases, cancer and diabetes (NCDs)] are currently the main causes of death and disability in adults in Chile and worldwide [1]. Although these conditions are observed in adulthood, there is now consistent evidence that NCDs originate in early life [first 1000 days (from -1 to + 2 years of life)] [2]. Several studies have shown that maternal body mass index (BMI) before conception and during pregnancy predict future risk of obesity and associated metabolic conditions for both mother and offspring [3–5]. Weight gain during the first two years of life is critical, not only to ensure newborn survival but also to define NCD susceptibility in later life [6–9]. This is a sensitive period in which nutrients and other environmental factors may condition gene expression and determine future health and NCD risks [10]. Thus, what we do or fail to do during the first 1000 days window provides a unique opportunity to decrease life-time NCDs risk [11]. Targeting this age group has an important potential impact given the current limitations in effectiveness of adult interventions [12], the wide coverage of maternal and infant programs and the lower cost of using existing resources. Unfortunately, maternal and infant programs have not adapted fast enough to meet the new challenges derived from the epidemiological and nutrition transitions, and obesity and NCDs continue to increase in most countries.

In Chile in recent years maternal and infant health and nutrition programs have been recognized as key to enhance human social capital [13]. However, from a nutrition perspective, these efforts have been insufficient to address the emergent NCDs. Excessive weight gain during pregnancy as well as childhood obesity have not been reduced but rather they have steadily increased particularly among the poor; presently, one out of three pregnant women is obese and 52 % of first-grade children report excess weight [14–16]. These trends are partly explained by implementation failures as well as delays in incorporate new knowledge in order to orient plan of action. This is particularly relevant in terms of nutrition recommendations and monitoring systems in place; these have not been fully updated to meet present international standards for nutrient intakes set by the World Health Organization (WHO) and the Food and Agriculture Organization (FAO) [17, 18]. There are now new recommendations (regarding the quantity and nutritional quality of the maternal diet and physical activity pattern during pregnancy) [19, 20] and monitoring goals (for both weight gain and glycaemic control) [21, 22] to support adequate fetal growth and maternal health during pregnancy and lactation [23]. Despite this, coverage of actions is often insufficient, i.e. specified actions are not always delivered on time, health personnel are not properly trained and/or beneficiaries do not attend scheduled visits. Several nutrition interventions during pregnancy focused on diet and physical activity have demonstrated their efficacy on reducing excessive maternal weight gain [24]; however, these studies are designed as high-intensity interventions in small sample sizes; thus limiting their applicability in clinical practice [25]. Further research is needed to confirm the effectiveness of low-intensity but high-coverage interventions on maternal and offspring outcomes and to assess the feasibility and ability of health care systems to deliver these interventions [26–28]. Thus, we propose a cluster randomized control trial (CRCT) [Chilean Maternal and Infant Nutrition Cohort Study (CHiMINCs)] to assess the impact of a low-intensity and high-coverage nutrition intervention by enhancing existing nutrition health care standards and practices at the primary health care level. We aim at increasing the proportion of women who achieve healthy weight gain and an adequate glycaemic control during pregnancy and the proportion of offspring who achieve a healthy growth during the first year of life.

## Methods/design

### Trial design

This is a CRCT designed as a public health "program effectiveness" trial (Fig. 1). The proposed intervention will be delivered through the national health system under standard operating conditions, thus no extraordinary resource-intensive measures to secure uptake are unnecessary. The cluster units will be 12 primary health care centers (PHCCs) in two counties in the South-East of Santiago randomly allocated to: 1) enhanced implementation of nutrition health care standards (intervention group) or 2) routine care (control group). The desired outcomes will be the achievement of adequate weight gain at the end of the pregnancy, glycaemic control at 24-28 weeks of pregnancy and healthy infant growth at one year of age. Pregnant women from PHCCs randomized to the intervention will receive weight gain monitoring, diet and PA counseling-support and BF promotion from the first prenatal visit (<15 weeks) to 12 months postpartum. Pregnant women who attend control PHCCs will receive routine antenatal care according to national guidelines [29].

**Fig. 1 Fig1:**
[figure not shown]
Flow chart for cluster randomized controlled trial comparing a normative nutrition intervention for pregnant women in public health care centers with usual care

### Participants

Inclusion criteria for the clusters will be PHCCs from the two major urban counties of South-East Health Area of Santiago with > 400 deliveries yearly in order to achieve timely recruitment [La Florida (n = 5) and Puente Alto (n = 7)]; however, if we experience administrative or technical difficulties, we will consider replacing them with 4 smaller PHCCs. The unit of analyses will be mothers and their offspring. Women seeking care before 15 weeks of pregnancy, residing within catchment area of selected PHCCs and who are not planning to move in the next two years will be invited to participate in the study. Pregnant women classified during the first visit as high risk according to the norms of the Chilean Ministry of Health (Age <16 or >40 years; Medical conditions that exist before pregnancy, (hypertension, diabetes insulin dependent, kidney or heart chronic disease, drug abuse); Previous pregnancy-related issues (neonatal/fetal death, multiple abortions, birthweight < 2500 g or > 4500 g, premature delivery, birth defects, hospitalization due to hypertension or preeclampsia, previous uterine surgery, RH isoimmunisation; gestational diabetes mellitus); Pregnancy-related issues (multiple gestation, vaginal bleeding, pelvic mass**))** and/or underweight (BMI < 18.5 kg/m^2^) will be excluded. Other conditions that may affect either weight and/or glycaemic control during pregnancy or lactation and infant growth (i.e. severe depression, severe infections, injuries and trauma, congenital malformations) will not be considered as exclusion criteria. We have chosen to record these conditions and consider them in a secondary analysis.

### Recruitment and randomization

We will invite each of the 12 PHCCs to participate in the study using regular health service channels. We plan to randomly allocate half of the 12 PHCCs to the intervention arm of the study and half to the control group. Randomization will be done prior to recruitment of participants. All pregnant women who attend these PHCCs and fulfill enrollment criteria will be invited to participate in this study by the PHCCs midwives at their first visit; inclusion criteria will be checked and an informed consent will be sought from those who express an interest in the study. We expect to complete participant recruitment by the end of the first year of study (April 2015).

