### Intervention

Overall, the CHiMINCs intervention is a low-intensity intervention designed to support the implementation of evidence-based guidelines by enhancing the uptake of existing programs (Table 1). The intervention for the intervened PHCCs has two main components: 1. Training to professionals: all midwives, dietitians and nurses will be trained on updated references, maternal weight gain assessment, use of charts, referral criteria to dietitian, dietary and physical activity recommendations, and how to communicate nutrition messages effectively. For this component several activities have been designed: one-day course, online refreshments (email and web page: http://www.chimincs.cl/), manual of procedures, technical support by the study coordinator, short brochure with nutrition messages, installation of a computer-assisted system for maternal weight monitoring based on IOM guidelines for weight gain during pregnancy in midwives´ consultation rooms. 2. Actions: *i.* Pregnant women at the first prenatal visit will be counseled regarding an optimal gestational weight gain range based on their pre-pregnancy nutritional status. At each routine midwife visit (mean prenatal visits in Chile = 6) weight gain will be assessed using the computer-assisted system for maternal monitoring and education and feedback about weight gain will be provided. Second, at each midwife visit pregnant women will receive advice about at least two of following nutrition messages (previously defined as more relevant by health professionals in a qualitative study): avoid the consumption of sugar-sweetened beverages (including fruit juice); restrict the consumption of white bread to two pieces/day; replace fatty meats (pork, veal, lamb) by lean meat (poultry, turkey) and fish; eat a variety of vegetables and fruits each day (at least 5 portions), in place of foods higher in fat and calories; antenatal breastfeeding promotion; invitation to physical activity classes. Third, midwife will refer pregnant women to dietitian according to defined criteria: gain more than 3 kg at the first trimester independently of their baseline nutritional status; gain more than 3, 2 and 1.5 kg at the second and third trimesters for normal, overweight and obese pregnant women at baseline, respectively. *ii.* A physical activity program for pregnant women of moderate-intensity exercise lasting 60 min and performed three times per week will be delivered at each PHCC supervised by licensed physical activity instructors. Each session will consist of 30 min of aerobic exercise of moderate-intensity (walking, dancing), 10 min of strength exercises and 10 min of stretching and elongating exercises.

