### Ethical approval

The protocol for this study has been approved by the Institute of Nutrition and Food Technology of University of Chile, the Catholic University of Chile, and the South-Eastern Health Service Ethics committees. Potential participants will be provided with detailed information by the project field staff on the nature and relevance of the trial and the actions involved if they agree to participate. Potential participants will then be asked to sign a written consent form.

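### Women are recruited after centre allocation by midwives who, in the intervention arm, know it, and centre replacement is not limited to before the draw, so enrolment may differ between arms

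*Protocol article*

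**What the plan says.** All places are in the protocol article.

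- **Order of events (Recruitment and randomization).** "We plan to randomly allocate half of the 12 PHCCs to the intervention arm of the study and half to the control group", and "Randomization will be done prior to recruitment of participants".
- **Who recruits (same section).** All attending women who "fulfill enrollment criteria will be invited to participate in this study by the PHCCs midwives at their first visit". After that, "inclusion criteria will be checked and an informed consent will be sought from those who express an interest in the study"; the sentence does not say by whom.
- **What intervention-centre midwives know (Intervention).** In those centres "all midwives, dietitians and nurses will be trained on updated references, maternal weight gain assessment, use of charts, referral criteria to dietitian". A weight-monitoring system is installed in their consultation rooms, and counselling on weight gain starts at the first prenatal visit, the visit at which women are invited.
- **Who informs women (Ethical approval).** "Potential participants will be provided with detailed information by the project field staff", after which women are asked to sign. Whether these staff are blind to the arm is not stated.
- **Replacement of centres (Participants).** After setting a criterion of more than 400 deliveries a year, the article adds: "if we experience administrative or technical difficulties, we will consider replacing them with 4 smaller PHCCs". It gives no timing relative to randomisation, no rule for the arm of a substitute, and no rule for analysing a replaced centre.
- **Analysis (Statistical methods).** The primary analysis is by allocated group, with covariate adjustment if baseline imbalance appears. Blinding is stated for the statisticians only.

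**The concern.** In a cluster trial, the draw makes the centres comparable. It makes the women comparable only if enrolment within centres does not depend on the arm. Here identification, eligibility checks and consent all follow the draw, and the person who opens the conversation in an intervention centre also delivers the intervention. Women more inclined to manage their weight might then enrol more readily in one arm than in the other.

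The resulting bias falls directly on the first maternal primary outcome, adequate weight gain, and a larger sample does not reduce it. The replacement clause raises the same issue one level up: if a centre could leave after its arm is known, the set of centres compared would no longer be the set that was randomised.

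**Working it through.** The article gives no figure for this point, so there is none to reproduce. The check has three parts.

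**1. Do the stated steps leave room for arm-dependent enrolment?**

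- The target is 200 women per centre (Sample size), from centres with more than 400 deliveries a year (Participants), with recruitment expected to finish by the end of the first study year. Exclusions and late attendance account for part of the gap, but the enrolled women are a subset of those attending.
- One eligibility item, not planning to move in the next two years, rests on the woman's own statement.
- Pre-pregnancy weight, which determines the weight-gain band used for the outcome, is taken from records and by direct questioning at recruitment (Data collection), and so after allocation.
- Analysis by allocation covers only women who enrolled. Adjustment can address measured covariates, but not motivation.

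**2. How large could the effect be?** This is an illustration; the uptake figures are assumptions.

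- Rate of adequate gain: p = 0.50 in both arms, the rate assumed under Sample size, with no true effect.
- Assumed uptake in one arm: 70% among women who will gain adequately and 60% among the others. In the other arm uptake is unrelated to outcome.
- Observed rate in the selected arm = 0.50 × 0.70 / (0.50 × 0.70 + 0.50 × 0.60) = 0.35 / 0.65 = 0.538.
- Spurious difference = 53.8% − 50% = 3.8 points.

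For an uptake ratio r, the difference at p = 0.50 is r/(r + 1) − 0.5:

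| Uptake ratio r | Spurious difference |
|---|---|
| 1.05 | 1.2 points |
| 1.10 | 2.4 points |
| 1.17 (70/60) | 3.8 points |
| 1.20 | 4.5 points |

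The article does not say whether its 20 % difference is relative or absolute:

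- relative, 50% to 60%: 3.8 / 10 = 38% of the target;
- absolute, 50% to 70%: 3.8 / 20 = 19% of the target.

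**3. What does that do to the false-positive rate?**

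- Inputs: 960 women per arm, 160 per centre (960 / 6), nominal two-sided 5% level.
- Design effect = 1 + 159 × ICC. This is 2.272 at ICC 0.008, and 1.013 at 0.00008, which is the printed 0.008 % taken literally.
- SE = √(0.5 × design effect / 960), which gives 0.0344 and 0.0230.
- Rejection rate for a bias b = 1 − Φ(1.96 − b/SE) + Φ(−1.96 − b/SE).

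| Bias b | ICC 0.008 | ICC 0.00008 |
|---|---|---|
| 2 points | 9% | 14% |
| 3 points | 14% | 26% |
| 3.8 points | about 20% | about 39% |
| 5 points | 31% | 59% |

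For 3.8 points: 0.038/0.0344 = 1.12 and 1 − Φ(0.84) ≈ 0.20; 0.038/0.0230 = 1.67 and 1 − Φ(0.29) ≈ 0.39.

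**Centre replacement.** No arithmetic applies. If a centre is replaced before the draw, the comparison is intact. If it is replaced after the draw, the substitute's arm is not the product of that randomisation, and the removed centre's women may be lost from the arm to which it was allocated.

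**The case against.** The case on the other side is substantial, and much of it stands.

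- **Midwives choose whom to invite.** A reader might infer this, but the article says all eligible attendees are invited and gives midwives no discretion. The risk lies in how evenly the rule is applied, in unblinded eligibility checks and in who consents.
- **The sections on recruitment and on ethical approval contradict each other.** They need not: the midwife may invite, and field staff may then inform the woman and obtain consent. The ethics section assigns no eligibility check to anyone. What remains is that the article does not say who checks criteria, or whether field staff know the arm.
- **Centres will be swapped after allocation.** The article does not say so. The clause sits among the cluster inclusion criteria, and replacement at centre selection is a natural reading. Nor does the text show that difficulties would be more frequent in intervention centres. The smaller size of the substitutes is an explicit exception to a threshold set for timely recruitment, not an error.
- **Exercise classes act as an inducement to enrol.** No section makes consent a condition for attending them, so this is not established.
- **Randomising before recruiting is a flaw.** It is usual where staff must first be trained, and is not wrong in itself. The weakness is its combination with unblinded recruiters and individual consent.

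It is also fair to say that the uptake rates are assumed, and that adjustment for baseline imbalance gives partial protection on measured covariates. Neither point removes the mechanism.

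**Conclusion.** The point holds in a limited form. The stated sequence allows enrolment to depend on the arm, and the stated analysis cannot undo that. The documents do not show that such selection will occur, so the size is conditional: with uptake ratios of 1.05 to 1.20 in one arm only and a 50% base rate, the spurious difference is 1.2 to 4.5 points. At 3.8 points it is 38% or 19% of the target, depending on how the 20 % difference is read, and the false-positive rate is about 20% at ICC 0.008.

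On replacement, the finding is only that the clause lacks a time limit. Unless a swap follows the draw, the randomised centres remain the compared clusters; it is the women enrolled within them whose comparability is at risk.

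**What to change.** 1. State that centres may be replaced only before the allocation draw. After it, each centre stays in its allocated arm and its enrolled women stay in the analysis.
2. Identify eligible women from the electronic first-visit records. Have the project field staff, rather than the intervention midwives, confirm eligibility and seek consent with one common script in both arms, blind to arm where feasible. State these roles consistently in the sections on recruitment and on ethical approval.
3. Log and report eligible, invited and consenting women by arm, with baseline characteristics.

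Optional, subject to ethics agreement: a sensitivity analysis of weight gain in all record-eligible women, using de-identified records.

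The cost is a few sentences, small logistic work and one data extract; electronic records and field staff are already part of the plan. The optional analysis costs more, because it uses records of women who did not consent. Field staff may not be fully blind, so these steps reduce the risk and make it visible but do not remove it.

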### Intervention

Overall, the CHiMINCs intervention is a low-intensity intervention designed to support the implementation of evidence-based guidelines by enhancing the uptake of existing programs (Table 1). The intervention for the intervened PHCCs has two main components: 1. Training to professionals: all midwives, dietitians and nurses will be trained on updated references, maternal weight gain assessment, use of charts, referral criteria to dietitian, dietary and physical activity recommendations, and how to communicate nutrition messages effectively. For this component several activities have been designed: one-day course, online refreshments (email and web page: http://www.chimincs.cl/), manual of procedures, technical support by the study coordinator, short brochure with nutrition messages, installation of a computer-assisted system for maternal weight monitoring based on IOM guidelines for weight gain during pregnancy in midwives´ consultation rooms. 2. Actions: *i.* Pregnant women at the first prenatal visit will be counseled regarding an optimal gestational weight gain range based on their pre-pregnancy nutritional status. At each routine midwife visit (mean prenatal visits in Chile = 6) weight gain will be assessed using the computer-assisted system for maternal monitoring and education and feedback about weight gain will be provided. Second, at each midwife visit pregnant women will receive advice about at least two of following nutrition messages (previously defined as more relevant by health professionals in a qualitative study): avoid the consumption of sugar-sweetened beverages (including fruit juice); restrict the consumption of white bread to two pieces/day; replace fatty meats (pork, veal, lamb) by lean meat (poultry, turkey) and fish; eat a variety of vegetables and fruits each day (at least 5 portions), in place of foods higher in fat and calories; antenatal breastfeeding promotion; invitation to physical activity classes. Third, midwife will refer pregnant women to dietitian according to defined criteria: gain more than 3 kg at the first trimester independently of their baseline nutritional status; gain more than 3, 2 and 1.5 kg at the second and third trimesters for normal, overweight and obese pregnant women at baseline, respectively. *ii.* A physical activity program for pregnant women of moderate-intensity exercise lasting 60 min and performed three times per week will be delivered at each PHCC supervised by licensed physical activity instructors. Each session will consist of 30 min of aerobic exercise of moderate-intensity (walking, dancing), 10 min of strength exercises and 10 min of stretching and elongating exercises.

**Table 1 Tab1:** Nutrition intervention

1.	Training on weight monitoring and delivery of messages for health professionals:
	a. 1-day course for dietitians, midwifes and nurses: revision of references, maternal and offspring nutrition assessment, use of charts, referral criteria to dietitian, dietary recommendations, how to communicate nutrition messages effectively
	b. Online re-training (email and web page)
	c. Procedural manual
	d. Technical support by the study coordinator
	e. Short brochure with nutrition messages
2.	Installation of a computer-assisted system for maternal weight monitoring based on IOM (Institute Of Medicine) guidelines in midwives´ consultation rooms
3.	At each midwife visit (pregnant women):
	a. Assessment of maternal weight gain. Education and feedback about weight gain.
	b. Delivery of at least two nutrition messages: Avoid the consumption of sugar-sweetened beverages (including fruit juice); Restrict the consumption of white bread to two pieces/day; Replace fatty meats (pork, veal, lamb) by lean meat (poultry, turkey) and fish; Eat a variety of vegetables and fruits each day (at least 5 portions), in place of foods higher in fat and calories; Breastfeeding promotion; Invitation to physical activity classes.
	c. Timely referral to dietitian according to defined criteria
4.	Physical activity program for pregnant women of moderate-intensity exercise supervised by physical activity instructors lasting 60 min and performed three times per week.

